## **6.6 Follow-up of subjects withdrawn from treatment**

Patients withdrawn from treatment will be asked if they will continue completing the questionnaires and if their medical record may be checked for reported toxicity and progression. Patients will be asked for oral and written informed consent.

## **6.7 Premature termination of the study**

A predefined interim analysis will be performed based on tumor volume as described in section 8.3. No premature termination of the study is expected due to safety issues, because the regimens have been used in practice before with limited toxicity and radionecrosis.

## 7. SAFETY REPORTING

### 7.1 Temporary halt for reasons of subject safety

In accordance to section 10, subsection 4, of the WMO, the sponsor will suspend the study if there is sufficient ground that continuation of the study will jeopardize subject health or safety. The sponsor will notify the accredited METC without undue delay of a temporary halt including the reason for such an action. The study will be suspended pending a further positive decision by the accredited METC. The investigator will take care that all subjects are kept informed.

### 7.2 AEs, SAEs and SUSARs

#### 7.2.1 Adverse events (AEs)

Adverse events are defined as any undesirable experience occurring to a subject during the study, whether or not considered related to re-irradiation treatment. All adverse events reported spontaneously by the subject or observed by the investigator or his staff will be recorded. Since any consequences of the radiotherapeutic treatment are expected to occur shortly after the radiation, AEs will only be reported until 30 days after the last fraction. Only AE's of grade 3 or higher will be reported, as treatment discomfort is inherent to this population. In addition, toxicity will already be registered as part of the study. Adverse events and their grading in glioma patients undergoing radiotherapy are summarized in Appendix 2.

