## 1. INTRODUCTION AND RATIONALE

### 1.1 Recurrent glioma and radiotherapy schedules

The diagnosis of high grade glioma is usually associated with an extremely poor prognosis, with a median overall survival time (mOS) for glioblastoma (GBM) patients of 14.6 months [1, 2]. Despite multimodality treatments, the local recurrence rate persists to be high (nearly 90% within 2 years) [1, 3]. Additionally, primary WHO grade II gliomas will eventually recur as a high grade glioma at a median of 61 months after primary treatment [4, 5]. Brain tumors have the highest average number of years of life lost of all cancers at 20.1 years, for example compared to prostate cancer at 6.1 years [6].

No standard salvage treatment for this orphan disease has been defined [4, 7, 8]. Next to re-resection and chemotherapy, re-irradiation (ReRT) can be considered as a safe and effective option, leading to mOS ranging from 7.7 to 11.5 months from ReRT start [9–15]. Next to re-resection and chemotherapy, re-irradiation (ReRT) can be considered as a safe and effective option, leading to mOS ranging from 7.7 to 11.5 months from ReRT start. Hypofractionated re-irradiation is shown to be safe and effective in earlier studies: no early or late toxicities above grade 2 (not requiring medical intervention), according to the CT-CAE criteria were observed. Acute toxicity observed in earlier studies included fatigue, headaches, nausea and alopecia and skin erythema. In one study, this was noted in 15% of the patients, but was all < grade 2. Late toxicity includes radionecrosis, this was observed in few patients. In a study by Combs et al, in only 1 out of 233 patients radiation induced necrosis was radiographically diagnosed and histologically confirmed and no other severe early or late side effects above grade 2 could be documented. Pinzi et al observed radiation necrosis in 6% of patients with large volume lesions and this was associated with neurological deterioration. Radionecrosis data reported in the literature indicate an average of 5-14%.

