#### 7.2.2 Serious adverse events (SAEs)

A serious adverse event is any untoward medical occurrence or effect that

- results in death.
- is life threatening (at the time of the event).
- requires hospitalization or prolongation of existing inpatients' hospitalization.
- results in persistent or significant disability or incapacity.
- is a congenital anomaly or birth defect.
- any other important medical event that did not result in any of the outcomes listed above due to medical or surgical intervention but could have been based upon appropriate judgment by the investigator.

An elective hospital admission will not be considered as a serious adverse event.

The investigator will report all SAEs to the sponsor without undue delay after obtaining knowledge of the events. However, patients with recurrent glioma have a poor life expectancy. Therefore, a significant proportion of patients will die within the study duration of 1 year after radiotherapy. The SAE sensitive period will be up until 30 days after last ReRT fraction to account for treatment related effects. Expected SAEs are hospitalization,

persistent or significant disability or incapacity, or death due to glioma progression. These expected SAEs will be reported every year in a line listing.

The sponsor will report the SAEs through the web portal *ToetsingOnline* to the accredited METC that approved the protocol, within 7 days of first knowledge for SAEs that result in death or are life threatening followed by a period of maximum of 8 days to complete the initial preliminary report. All other SAEs will be reported within a period of maximum 15 days after the sponsor has first knowledge of the serious adverse events.

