### **8.1.4 Toxicity**

Toxicity will only be assessed in the experimental group. Analyses of radiotherapy toxicity will be performed in all patients who received at least one fraction. Acute events occurring from start of radiotherapy until 90 days and late events occurring from 91 days after end of radiotherapy will be presented. Further analyses of treatment toxicity will present the grade 3 to 5 acute or late side effect by treatment arm. The time to occurrence of any severe late side effects and separately radionecrosis (distinguishing symptomatic and asymptomatic) will be estimated by cumulative incidence. The time to severe late side effects will be calculated from the time of start of radiation treatment to the first evidence of any grade 3-5 late side effects. Patients alive without grade 3-5 late toxicity will be censored at the date of last

follow-up, patients who died without experiencing late grade 3-5 side effects will be assessed as competing risk at the time of death.

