## **8.3 Interim analysis**

Six months after inclusion of every 10 patients an interim analysis will be performed to review the toxicity data. If the toxicity is unexpectedly high in large tumors (65-125cc), the maximal tumor diameter will be modified to 5 cm (reflecting a spherical tumor of 65 cc). The detailed interim analyses are not made available to trial participants.

Sequential boundaries will be used to monitor dose-limiting toxicity rate. Full follow-up for acute toxicity is defined as 90 days after last irradiation fraction. Full follow-up for radionecrosis is defined as after the MRI at 6 months. This is a Pocock-type stopping boundary that yields the probability of crossing the boundary at most 0.05 when the rate of dose-limiting toxicity is equal to the acceptable rate 30, 20 or 10% depending on adverse event grading [45].

The research team will be responsible for the interim analysis. The accrual of patients with a tumor with a diameter >5 cm will be halted if excessive numbers of dose-limiting toxicities are seen, that is, if the number of dose-limiting toxicities is equal to or exceeds  $b_n$  out of  $n$  patients with full follow-up (Table 4.1, 4.2 and 4.3). No more interim analyses will be performed if accrual of patients with a tumor volume of >5 cm (reflecting a spherical tumor of 65 cc) is halted based on the above, if after 4 iterations of interim analyses, no excessive numbers of dose-limiting toxicities are seen, as mentioned above or when inclusion is completed without excessive dose-limiting toxicities. In any of these cases, the METC that gave a favorable opinion will be notified.

**Table 4.1 The maximal tumor volume will be modified if the number of dose limiting grade 3 to 5 toxicities is equal to or exceeds  $b_n$  out of  $n$  patients with completed follow-up. This boundary is equivalent to testing the null hypothesis, after each patient, that the event rate is equal to 0.3, using a one-sided level 0.017041 test.**

|                         |    |    |    |    |    |    |    |    |    |    |    |    |    |    |    |    |    |    |    |    |
|-------------------------|----|----|----|----|----|----|----|----|----|----|----|----|----|----|----|----|----|----|----|----|
| Number of Patients, $n$ | 1  | 2  | 3  | 4  | 5  | 6  | 7  | 8  | 9  | 10 | 11 | 12 | 13 | 14 | 15 | 16 | 17 | 18 | 19 | 20 |
| Gr 3-5 Boundary, $b_n$  | -  | -  | -  | 4  | 5  | 5  | 6  | 6  | 7  | 7  | 8  | 8  | 9  | 9  | 10 | 10 | 10 | 11 | 11 | 12 |

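### AE and SAE reporting both end 30 days after the last fraction, before the protocol's own window for late toxicity opens, so a serious treatment-related late event has no individual expedited report

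*Protocol*

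**What the plan says.** Section 7.2.1 limits individual AE reporting in time: "AEs will only be reported until 30 days after the last fraction". It gives the reason in the same sentence: "Since any consequences of the radiotherapeutic treatment are expected to occur shortly after the radiation". It restricts reporting to grade 3 or higher and notes that toxicity is registered separately as a study outcome.

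Section 7.2.2 sets the same limit for serious events: "The SAE sensitive period will be up until 30 days after last ReRT fraction to account for treatment related effects". The duty to inform the sponsor promptly and the deadlines to the METC ("within 7 days of first knowledge for SAEs that result in death or are life threatening", and 15 days for other SAEs) attach to SAEs only.

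Other sections describe the timing of harm differently:

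- Section 1.1: "Late toxicity includes radionecrosis, this was observed in few patients".
- Section 8.1.4: "late events occurring from 91 days after end of radiotherapy will be presented", with a cumulative-incidence analysis of grade 3-5 late effects and, separately, of radionecrosis.
- Section 8.3: "Full follow-up for acute toxicity is defined as 90 days after last irradiation fraction" and "Full follow-up for radionecrosis is defined as after the MRI at 6 months".
- Appendix 2 lists grades 4 (life-threatening) and 5 (death) for CNS necrosis.

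Section 7.4 states that no DSMB will be set up.

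**The concern.** The reason given for the 30-day limit is at odds with the rest of the protocol, which treats radionecrosis as a late effect and builds its toxicity analysis and interim monitoring around that. The SAE period is said to be there to capture treatment-related effects, yet it closes before the late ones can begin.

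What is at stake is patient safety during the trial, not the primary survival comparison. For a serious late event caused by re-irradiation, the protocol creates no case-level duty to tell the sponsor and no METC deadline. The only routine review left is an aggregate count kept by the research team.

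**Working it through.** No design figure governs the reporting window, so the check compares time windows, follows one event through the rules, and then gauges how many patients could be affected.

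**1. The windows side by side**

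| Window | Limit | Section |
|---|---|---|
| AE reporting ends | day 30 after last fraction | 7.2.1 |
| SAE period ends | day 30 after last fraction | 7.2.2 |
| Acute toxicity follow-up complete | day 90 after last fraction | 8.3 |
| Late events begin | day 91 after end of radiotherapy | 8.1.4 |
| Radionecrosis follow-up complete | after the 6-month MRI | 8.3 |
| Scheduled toxicity calls end | week 52 from start, or progression if sooner | 6.2 |

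- Reporting closes to late window opens: 91 − 30 = 61 days.
- Acute window left uncovered after treatment: 90 − 30 = 60 days, two thirds of it.
- Reporting closes to 6-month MRI, assuming the MRI is at week 26 (day 182 from start) and the last fraction no later than day 14: 182 − 14 − 30 = 138 days or more.

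No event in the late window can fall inside the AE or SAE window.

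**2. One event followed through the rules**

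Take a grade 4 CNS necrosis 120 days after the last fraction. Since 120 > 30, it is outside both reporting periods. Since 120 ≥ 91, it is a late toxicity under 8.1.4. It is recorded as an outcome, enters the cumulative incidence, and counts toward the 8.3 boundaries. It triggers no individual SAE report to the sponsor and no 7- or 15-day METC report, and it is not among the SAEs in the annual report (10.4).

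**3. What the interim count does instead**

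- Looks are made six months after each 10 inclusions and end after four iterations. Assuming blocks of 10 counted over all of arm 1: 4 × 10 = 40 patients, leaving 66 − 40 = 26 (26/66 = 39%) without a look.
- Table 4.3 allows a 10% grade 5 rate. Its boundary of 4 at n = 10 reproduces: with rate 0.1, P(X ≥ 4 of 10) = 0.0128, below the stated level 0.015673, while P(X ≥ 3 of 10) = 0.0702 is above it. The whole table reproduces, with an overall crossing probability of 0.0496 if checked after every patient.
- At the look on 10 patients, three fatal toxicities therefore do not cross the grade 5 boundary. Alone they do not cross Table 4.2 (6 of 10) or Table 4.1 (7 of 10) either.
- Under 8.3 the METC is notified when monitoring ends: the large-tumor stratum is closed, four iterations are done, or inclusion is complete. The only action tied to the boundaries is a smaller maximum tumor diameter.

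**4. Scale, using the protocol's own cited rates and 66 patients**

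- Radionecrosis, grade not stated, 5-14% (section 1.1): 66 × 0.05 = 3.3 and 66 × 0.14 = 9.2, so about 3 to 9 patients.
- Pooled grade 3 or higher toxicity of all kinds, 4-10% (section 1.3): 66 × 0.04 = 2.6 and 66 × 0.10 = 6.6, so about 3 to 7 patients.

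The first range includes asymptomatic necrosis and the second includes acute events. The number of serious late events is some unknown part of these.

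**The case against.** The strongest defence is that late toxicity is well covered outside section 7.2. Spontaneously reported and observed AEs are recorded. Toxicity is asked about by telephone to week 52 or progression, and clinicians record it at regular consultations. Late grade 3-5 effects are analysed with death as a competing risk, and late radionecrosis counts toward interim boundaries, including separate ones for grades 4-5 and 5. Section 7.1 requires the sponsor to suspend the study and inform the METC if safety demands it, and the annual report has room for other problems. Section 7.2.2 also gives a fair reason for a short window: many patients will die of their tumor within a year.

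Much of this stands. A reader might infer that a late fatal necrosis is never recorded or reviewed, or that necrosis before the 6-month MRI is not counted. The documents support neither: the event is registered and counted, and the MRI marks when follow-up is complete, not when an event may occur. A reader might also apply the 30-43% in section 1.3 to all 66 patients and expect 20 to 28 cases. Those figures come from one series' stereotactic group (30%), from all late adverse events in another study (36%), and from the minority progression-free at 10 weeks in a third (43%), so they do not carry over. Nor does the dose comparison settle the risk: the boost has an EQD2 of 71 Gy against 48 Gy in the controls, but the surrounding zone has 41 Gy, which section 1.5 says could limit necrosis.

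What the defence does not supply is a case-level report. An outcome record carries no duty of prompt notice. Scheduled calls stop at progression, which section 6.2 accepts can be hard to tell from necrosis. A section 7.1 halt depends on the sponsor knowing of the cases. The flood of tumor deaths justifies excluding progression events, not treatment-related ones.

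**Conclusion.** The point holds as an internal contradiction with a safety consequence. Both 30-day limits are explicit, their stated rationale conflicts with sections 1.1, 8.1.4 and 8.3, and reporting ends 61 days before the late window begins. A serious treatment-related late event therefore has no individual SAE report and no METC deadline, with no DSMB as an alternative and interim looks reaching about 40 of 66 patients.

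The number affected is small and cannot be fixed from the protocol: some part of about 3 to 9 necroses of any grade, or of about 3 to 7 grade 3 or higher toxicities. This assumes that the cited rates apply to arm 1, that arm 1 reaches 66, and that looks are made per 10 patients. The 61-day gap depends on none of these. No toxicity endpoint or efficacy analysis is lost through the reporting limit.

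**What to change.** Reconcile 7.2.1 and 7.2.2 with 8.1.4 and 8.3 by amendment:

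- Keep the 30-day period for events unrelated to re-irradiation and for events due to glioma progression.
- Add that any event meeting the seriousness criteria of 7.2.2 and judged at least possibly related to re-irradiation, on the attribution scale already in Appendix 2, is reported as an SAE whenever the investigator learns of it during the 12-month active follow-up, including after progression. Seriousness, not CTCAE grade, should be the trigger, because Appendix 2 says SAEs are not assessed by CTCAE.
- In 7.2.1 remove only the clause about consequences appearing soon after radiation. The 30-day limit stands in the same sentence and has to be kept for the events above.

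The cost is one amendment and a few more SAE reports. No new visits are needed, but after progression the reports will rest on clinicians' regular consultations, because scheduled calls have stopped. The main downside is attribution: where necrosis and progression are hard to separate, investigators will have to make and document a judgement.

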#### 7.2.2 Serious adverse events (SAEs)

A serious adverse event is any untoward medical occurrence or effect that

- results in death.
- is life threatening (at the time of the event).
- requires hospitalization or prolongation of existing inpatients' hospitalization.
- results in persistent or significant disability or incapacity.
- is a congenital anomaly or birth defect.
- any other important medical event that did not result in any of the outcomes listed above due to medical or surgical intervention but could have been based upon appropriate judgment by the investigator.

An elective hospital admission will not be considered as a serious adverse event.

The investigator will report all SAEs to the sponsor without undue delay after obtaining knowledge of the events. However, patients with recurrent glioma have a poor life expectancy. Therefore, a significant proportion of patients will die within the study duration of 1 year after radiotherapy. The SAE sensitive period will be up until 30 days after last ReRT fraction to account for treatment related effects. Expected SAEs are hospitalization,

persistent or significant disability or incapacity, or death due to glioma progression. These expected SAEs will be reported every year in a line listing.

The sponsor will report the SAEs through the web portal *ToetsingOnline* to the accredited METC that approved the protocol, within 7 days of first knowledge for SAEs that result in death or are life threatening followed by a period of maximum of 8 days to complete the initial preliminary report. All other SAEs will be reported within a period of maximum 15 days after the sponsor has first knowledge of the serious adverse events.

### **7.3 Follow-up of adverse events**

All AEs will be followed until they have abated, or until a stable situation has been reached. Depending on the event, follow up may require additional tests or medical procedures as indicated, and/or referral to the general physician or a medical specialist.

### **7.4 Data Safety Monitoring Board (DSMB)**

A DSMB will not be established, due to the low risk of adverse events.

## 8. STATISTICAL ANALYSIS

### 8.1 Study parameter(s)

Planned statistical methods for the trial are presented in this chapter. Minor revisions to this statistical analysis plan are allowed. Final statistical analysis plan should be written prior to any formal analysis of the data and finalized prior to end of patient recruitment.

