### 3. STUDY DESIGN

The original 2019 RISING-trial (RISING trial A) was designed as an open label, randomized, non-inferiority, phase III trial with 1:1 allocation for 130 patients. In this trial 13 patients were included in the experimental arm and 16 patients were included in the control arm. The updated 2023 RISinG trial (RISING trial B) is designed as a phase II, multi-center, clinical trial with a historic control group. The additional recruitment period of this phase will be approximately 30 months with an active follow-up time of 12 months.

The 13 patients of the RISING trial A will be supplemented until a total of 66 patients is reached. These patients fulfilling the inclusion criteria will get the following treatment:

- Hypofractionated radiotherapy with SIB in 2 weeks  
4 fractions of 7.5 Gy SIB to the GTV  
And 4 fractions of 5.5 Gy to the CTV (GTV + 5mm margin).

We will compare the survival of this group with a retrospective control group of patients, subtracted from the retro-RISinG registry study, a multi-center retrospective nation-wide population based cohort study, in which details of patient-, tumor- and treatment-related data of all patients with a recurrence of a primary brain tumor since January 2002 up to December 2022 in the Netherlands will be collected. We will select 99 matched patients in total with the following treatment:

- Moderately hypofractionated radiotherapy in 2-3 weeks  
10 fractions of 3.5 Gy to the CTV (GTV + 5 mm margin)

An overview of the target volume definitions and dose prescriptions is presented in table A3 in section 1.8 of the Appendix.

This control group will be matched to the patients in the experimental arm on an individual level for:

1. Age;
2. Gender;
3. WHO-grade primary tumor;
4. Time interval in between first radiation and re-irradiation;
5. MGMT-status.

[figure not shown]

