## 4. STUDY POPULATION

### 4.1 Population

Patient enrollment in the experimental arm (arm 1) continues until 66 adult patients with recurrent gliomas eligible for re-irradiation are recruited **in total** (RISING A & B) in the participating hospitals. The recruitment period will be approximately 30 months with an active follow-up time of 12 months.

The control group of the original RISinG study (A) had 16 patients. An additional 83 patients will be selected from the retro-RISING study, a multicenter retrospective nation-wide population-based cohort study, in which details of patient-, tumor- and treatment –related data of patients with a recurrence of a primary brain tumor since January 2002 up to December 2022 in the Netherlands will be collected for arm 2. Out of the retro-RISING trial, we will select only the patients with a treatment schedule of 10x3.5Gy. These patients will be individually matched to the patients in the experimental arm.

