#### 8.1.1 OS and PFS

All statistical tests for the efficacy endpoint OS and PFS will be performed according to intention-to-treat (ITT) principle, which is the most unbiased method. Considering the trial being a non-inferiority trial, which is more sensitive to bias, a secondary per-protocol (PP) analysis will be done for OS [43]. The PP analyses will be performed on a “subset of patients who complied sufficiently with the protocol, such as exposure to treatment, availability of measures and absence of major protocol violations” according to the ICH E9 guidelines. The ITT analysis includes all participants. Start date of ReRT will be used as time is 0. Patients not known to have died during the study will be censored for OS at the day they were last known to be alive. Patients free from progression and alive at the last visit will be censored for PFS at the day of last assessment. Endpoints are measured from the first date of re-irradiation.

Distributions of OS and PFS will be estimated by the Kaplan-Meier method. The OS rates at one year, PFS rates at six months and medians of OS and PFS will be presented with two-sided 95% confidence interval(CI) computed using the log-log transformation.

To minimize the effect of confounding when estimating the difference between the treatment and retrospective control group, stabilized inverse probability of treatment weighting (SIPTW) using propensity scores will be applied when comparing the groups on OS and PFS.

Propensity scores will be estimated using logistic regression including important covariates for OS and PFS: primary histology, GTV, KPS and age.

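### Section 8.1 lets the analysis plan be locked as late as the end of recruitment, when survival of the historic controls is already largely observable, and nothing keeps those who match and weight controls unaware of it

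*Protocol*

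**What the plan says.** On timing, section 8.1 states: "Final statistical analysis plan should be written prior to any formal analysis of the data and finalized prior to end of patient recruitment". The sentence before it reads "Minor revisions to this statistical analysis plan are allowed", without saying what counts as minor.

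On the comparator, section 3 describes a nationwide registry in which data on patients with recurrence of a "primary brain tumor since January 2002 up to December 2022 in the Netherlands will be collected". Section 4.1 adds: "An additional 83 patients will be selected from the retro-RISING study". Of trial A, section 3 says: "In this trial 13 patients were included in the experimental arm and 16 patients were included in the control arm". The control group is therefore 83 + 16 = 99, against 66 experimental patients.

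On control selection, section 3 says: "This control group will be matched to the patients in the experimental arm on an individual level for" age, gender, WHO grade of the primary tumour, interval between the two courses of radiotherapy, and MGMT status.

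On adjustment, section 8.1.1 prescribes stabilized inverse probability of treatment weighting and adds: "Propensity scores will be estimated using logistic regression including important covariates for OS and PFS: primary histology, GTV, KPS and age". Section 8.1.1.1 prescribes a Cox model and the decision rule: the upper limit of the 90% confidence interval for the hazard ratio must not exceed 1.4.

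**The concern.** Finalizing the plan before recruitment ends is a reasonable safeguard when treatment is allocated at random and control outcomes have yet to occur. In this trial, choosing the controls is itself an analysis decision, and it is made among patients whose outcomes have mostly happened. A control set with shorter survival favours non-inferiority whatever happens in arm 1, so knowing control survival alone is enough to steer the result, knowingly or not.

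The bar on formal analysis does not bar looking at the data. No section says that those who select or weight controls work without outcome data. At stake is the primary conclusion: whether the one-sided 5% error behind the 1.4 margin still holds.

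**Working it through.** **The plan's own figure.** Inputs from section 4.4: one-sided alpha 0.05, power 0.80, true HR 0.90, margin 1.4, allocation 40:60, event proportion 0.8.

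- Events = (1.645 + 0.842)² / [0.4 × 0.6 × ln(1.4/0.9)²] = 6.183 / (0.24 × 0.4418²) = 131.96, so 132.
- Patients = 131.96 / 0.8 = 164.9, so 165, split 66 and 99.

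This agrees with section 4.4. The point below concerns timing and changes none of these numbers.

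**How much survival is observable at the permitted lock date.** Section 4.4 gives a 12-month event rate of 0.7. Exponential survival is an assumption. The registry closes in December 2022 and the 2023 design recruits for about 30 months, so a control treated on the last registry date has at least 2.5 years of elapsed time when recruitment ends.

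- Probability of death by 2.5 years = 1 − (1 − 0.7)^2.5 = 1 − 0.049 = 0.951.
- With 12-month rates of 0.6 and 0.8 it is 0.899 and 0.982.
- Controls treated earlier have had longer still.

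**What is fixed and what is open.**

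| Element | Status in the protocol |
|---|---|
| Matching factors (five) | Named, section 3 |
| Propensity covariates (four), logistic regression, stabilized weights | Named, section 8.1.1 |
| Cox model, margin, 90% interval rule | Named, section 8.1.1.1 |
| Matching algorithm: calipers, order, scheme for 99:66 | Not given |
| How matching and weighting combine | Not given |
| Weight handling | Not given |
| Meaning of a minor revision | Not given |
| Separation of control selection from outcomes | Not given |

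**Illustration of the possible effect.** Suppose the most favourable of k specifications is reported, each with one-sided error 5% and with pairwise correlation rho between their test statistics. The overall error is 1 − P(all k statistics fail to cross 1.645). Neither k nor rho is in the documents.

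For different control sets, rho can be approximated. The 66 experimental patients are shared, so their part of the variance is (1/66) / (1/66 + 1/99) = 0.6, and rho = 0.6 + 0.4 × (share of controls in common). If 83 are drawn at random from M eligible registry patients and the 16 trial A controls are always kept, the common share is (16 + 83²/M)/99.

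- M = 94: share 0.90, rho 0.96.
- M = 234: share 0.46, rho 0.78.
- M of about 790: share 0.25, rho 0.70.

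| rho | best of 2 | best of 3 | best of 5 |
|---|---|---|---|
| 0.96 | 6.2% | 6.8% | 7.7% |
| 0.90 | 6.8% | 8.0% | 9.5% |
| 0.78 | 7.6% | 9.5% | 12.1% |
| 0.70 | 8.0% | 10.3% | 13.5% |

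A simulation of control-set choice points the same way. It assumed true HR 1.4, 66 against 99 patients, control 12-month event rate 0.7, random candidate sets, unadjusted Cox models and 1,500 runs per setting. The registry pools of 110, 165 and 250 are also assumed. One set fixed in advance gave about 4% to 5% false non-inferiority, and the best of 3 sets gave about 7% to 9%.

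**The case against.** The strongest reply is that much is already fixed and the rest is ordinary detail for the statistical analysis plan. The first half stands: a reader might infer that the whole model is open, but the matching factors, covariates, weighting method, Cox model and decision rule are written down, and replacing the covariate set could hardly be called minor. The second half does not answer the point. The fault is not that details are missing, but that the protocol itself sets a lock date that does not precede access to control outcomes.

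Second, matching is individual, so the full set of 99 cannot exist before arm 1 is enrolled, and the plan must be final before the complete comparison can be run. That is real but partial protection, since the survival of the eligible registry pool can be seen without a finished matched set.

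Third, the registry data are described as still to be collected, and no section says that survival has been extracted or viewed. This stands: the documents show an opportunity that is not prevented, not a data-driven choice. Some control-type outcomes are nevertheless known. Section 1.1 reports overall survival by fractionation group in a published Utrecht and Groningen cohort of 121 re-irradiated patients. The documents do not say how far it overlaps the registry controls.

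Fourth, section 8.3 says "The research team will be responsible for the interim analysis", from which a reader might infer that the team follows arm 1 survival while choosing controls. The text does not support this: that review covers toxicity, involves no controls and compares no survival. It is no part of the case.

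**Conclusion.** The point holds as a poorly placed lock date with no separation between control selection and outcomes. About 95% of the latest-treated registry controls (90% to 98% for 12-month rates of 0.6 to 0.8) would be expected to have died by the permitted date, under exponential survival.

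The false non-inferiority rate could rise above 5%: to about 6% to 13.5% under assumed best-of-2 to best-of-5 selection with correlation 0.7 to 0.96. The upper end needs low correlation and deliberate picking among five specifications, so it is a worst case. A reader might take these figures as the actual error of the trial. They are not, because neither the number of specifications nor their correlation is documented and nothing shows that any such selection occurs.

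That the matching factors and the propensity covariates differ is a separate matter and adds no weight here. It only means that the final covariate set has to be settled as part of the lock.

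**What to change.** Change section 8.1 as follows.

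- Date and lock the control-selection and weighting specification now, before registry OS and PFS are released to anyone who selects or analyses controls. It should cover the matching algorithm (calipers, order, the 99:66 scheme), the final covariate set, how matching and weighting combine, and weight handling.
- Once arm 1 enrolment is complete, run the locked algorithm on a registry extract without OS and PFS to produce the control list. A fixed list today is not possible with individual matching, but a fixed algorithm is.
- Report any later change to this specification as a sensitivity analysis only, in place of the undefined allowance for minor revisions.
- Record which control outcomes the team has already seen, in particular those of trial A and of the published cohort.

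The cost is earlier writing of this part of the plan and one outcome-free data extract. The design stays at 165 patients and about 132 events.
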